## Abstract

Promoting a healthy sleep is a big challenge and becomes a strategic priority in public health, due to the severe consequences on children’s development and risk to psychiatric diseases. Interventions that promote healthy sleep, such as those that focus on the dissemination of behavioral and environmental recommendations of sleep hygiene with children, are presented as an alternative. Serious game design offers wide-reaching domains in health applications and is increasing in popularity, particularly with children and teens because of it’s potential to engage and motivate players differently from other interventions. This study aims to evaluate effects of serious game on sleep hygiene recommendations “Perfect Bedroom: learn to sleep well,” on sleep habits and sleep parameters of healthy children. This is an experimental, prospective and quantitative study. We will randomize children in experimental (*n* = 88) and no intervention groups (*n* = 88). The experiment has four stages (pre-intervention, intervention, post-intervention, and follow-up), which will count with participation of children and their parents/guardians. In the evaluation stages, the guardians will answer questionnaires and scales to assess sociodemographic and health data, sleep habits and sleep pattern of their child. The children themselves will answer the following: a scale to assess sleepiness levels, a questionnaire to evaluate the serious game and the game itself, will characterize their bedroom and the activities they perform before sleep, with strategies developed by researches. Intervention with experimental group conducted with the serious game “Perfect Bedroom” will happen twice a week, for 3 weeks in a row, resulting in six sessions of 50 min each. Inferential analysis will be conducted for comparisons between groups and intragroups to measure effect of intervention in primary outcomes (sleep habits) and secondary outcomes (sleep parameters). We expect that the intervention with this game can provide valuable evidence to a new approach in promoting healthy sleep habits, with applications in clinical, educational, and familiar settings, which could diminish future health issues and risk at psychiatric diseases, decreasing the social burden of treatments for these conditions in children.

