### Design and Procedures

It will be used an experimental, prospective, quantitative and randomized controlled trial to compare effects of game application on change of habits and parameters of sleep, besides what the users will be able to do by playing this serious game. In order to achieve that, the following steps will be conducted: (1) randomization of participants to allocate each one in experimental or control group; (2) use of a control group that should not be submitted to intervention, to infer highest internal validity; (3) intervention with experimental group, which will allow us to evaluate if there was any modification in the parameters evaluated, determining the validity of the intervention and (4) evaluation of participants at three distinct moments throughout the study, namely: pre-intervention, immediate post-intervention and follow-up assessment, after 4 weeks (Suresh, 2011).

After selecting the schools by convenience, experimental and control groups are selected by two processes of randomization. The first will select which classes will compose the experimental and control groups in each school, throughout a basic method of randomization that is flipping a coin; in other words, one situation will be associated with each side of coin (e.g., heads – control and tails – experimental) to determinate the assignment of each class. Second, the function “Randomly assign subjects to groups” in online software GraphPad^1^ will be used to allocate participants of each class with valid data for analysis to each group.

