The control group will follow the institution’s school activities defined on the school schedule. The only moments of contact with study staff will be during evaluation, pre-, post and following intervention, to assure a proper control condition, in accordance to our research question about intervention works (Holmes et al., 2018). Considering this, further control will be needed for the following factors: contact with research team limited only to evaluation periods to avoid confusing factors such as attention, warmth, or human relationships. In the evaluation stages, the guardians will answer questionnaires and scales to assess sociodemographic and health data, sleep habits and sleep pattern of their child. The children themselves will answer: a scale to assess sleepiness levels, a questionnaire to evaluate the serious game and the game itself, will characterize their bedroom and the activities they perform before sleep. Also, teachers will be informed only essential information about the study and will be instructed to not use the knowledge acquired about sleep in class during the period of the research.

After completion of the intervention, the last two steps, post intervention evaluation and follow-up evaluation, will be conducted after 4 weeks. In these stages sleep habits and sleep patterns will be re-evaluated by the parents. Additional encounters 1 week after each evaluation will be provided to clarify any doubts about filling in the sleep diary and/or use of actiwatch. During these steps the children will be required to answer the Pictorial Sleepiness Scale of Maldonado and to characterize their bedroom and any activities that they perform before sleep at night (**Figure 2**). Thus, there will be three meetings with parents/guardians during evaluation steps, with three more other encounters to elucidate any doubt about assessments. Missing data will result in individuals being excluded without outcome.

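### The protocol names conflicting units of allocation (child, class, then children within class) and limits the last step to children with valid data

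*Protocol article*

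**What the plan says.** The Abstract takes the child as the unit ("We will randomize children in experimental") and gives 88 children per group. In Design and Procedures, the first listed step agrees: "randomization of participants to allocate each one in experimental or control group".

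The next paragraph of that section says that "experimental and control groups are selected by two processes of randomization".
- First process: "The first will select which classes will compose the experimental and control groups in each school". A coin is flipped "to determinate the assignment of each class".
- Second process: a GraphPad function "will be used to allocate participants of each class with valid data for analysis to each group".

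Four other statements bear on this:
- Design and Procedures also states: "Missing data will result in individuals being excluded without outcome".
- Materials and Equipment drops from the analysis any child absent from the sessions, although that child goes on taking part.
- Design and Procedures places a workshop for experimental-group parents in the pre-intervention stage, where the sleep diary and actiwatch are also handed out.
- Participants gives classes of 23 to 28 children, and 88 per group from alpha 5%, effect size 0.5 and power 95%.

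**The concern.** The unit of allocation determines the analysis, the sample size and whether the two arms mix in one classroom. Here the text names the child, then the class, then the child within the class, and does not say which assignment governs. Staff could follow incompatible procedures and each be faithful to the text.

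The last step is also limited to children whose data are valid for analysis. If that is judged after the arm is known, the analysed groups are formed partly by who supplied complete data, and completeness may differ between parents who attended a workshop and parents who did not. No later analysis fully repairs that.

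**Working it through.** **1. Can both steps fix the arm?**
- If the software governs, children of one class go to both arms and the class coin has no effect. Control children then sit in the same class as players, although Design and Procedures limits controls' contact with staff to the evaluations and tells teachers not to use sleep knowledge in class.
- If the coin governs, all children of a class already have an arm, so the software has nothing left to allocate. It can only pick which children are analysed, from those with valid data.

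No reading lets both steps do what the text says.

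**2. When is validity known?** Diaries and actigraphy run for 10 days (Sleep Diaries; Actigraphy). The experimental-group workshop is described in the same stage, directly after these are handed out. The arm therefore appears to be known before the 10-day baseline record can be complete. If valid data means only eligibility or questionnaire data, the step could come earlier.

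**3. What the 88 assumes.** For two independent groups with d = 0.5, alpha = 0.05 and power = 0.95, the noncentral t calculation gives 88 per group one-sided (power 95.1%), which matches the plan. Two-sided it gives 105, and power at 88 is 91.0%. So 88 is the one-sided figure for independently randomised children, with no class term.

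**4. Number of classes.** It is not stated. 176/28 = 6.3 and 176/23 = 7.7, so about 6 to 8 full classes. Eight classes, 4 per school, is assumed below, with 3 per school as the alternative.

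**5. Balance, if each class has its own unpaired flip.**
- 4-4 split of 8 classes: C(8,4)/2^8 = 70/256 = 27%.
- 6-2 or more uneven: 2(1 + 8 + 28)/256 = 74/256 = 29%.
- A school of 4 classes wholly in one arm: 2/2^4 = 0.125. At least one of two schools: 1 - 0.875^2 = 23%.
- A school of 3 classes: 2/2^3 = 0.25. At least one of two: 1 - 0.75^2 = 44%.
- With 7 classes an equal split is impossible.

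**6. Power, if the class is the unit.** Design effect = 1 + (m - 1) × ICC. The ICC is not in the document; 0.01 to 0.10 is assumed.
- m = 23, ICC = 0.01: 1 + 22 × 0.01 = 1.22; effective n per group 88/1.22 = 72.1; one-sided power about 91%.
- m = 28, ICC = 0.10: 1 + 27 × 0.10 = 3.70; effective n per group 88/3.70 = 23.8; one-sided power about 53%.

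These use the normal approximation, before the further loss of degrees of freedom from having few classes.

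**The case against.** Several stronger readings are tempting, and the document does not support them.

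- **Allocation concealment is broken.** A reader might infer this from the valid-data condition. But eligibility is itself checked by questionnaires and scales, so valid data may mean baseline or eligibility data, and software allocation after baseline does not break concealment. A purely random draw of children for analysis would cost precision without adding bias; any bias would come from excluding incomplete cases. The words on validity for analysis and the workshop's timing lean the other way but do not settle it, and the flow chart, which may give the order, is not shown.
- **The flips are independent.** The text speaks of both groups in each school, which could mean one flip per pair of classes. A one-arm school could not then occur, and the imbalance figures would not apply. This stands, so those figures are conditional.
- **Control children will share a class with players.** Sessions are held in class time while controls keep to the school schedule, which fits delivery by class better. This is one branch of the contradiction, and the less likely one.

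Simple randomisation is also valid in itself, so chance imbalance alone would be a matter of efficiency. Nor is this a detail that an article leaves to the full protocol: what the article states conflicts with itself. None of these objections removes the conflict of unit.

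**Conclusion.** The point holds as a contradiction in stated rules. The Abstract and Design and Procedures give units of allocation that cannot all apply, and the last step depends on undefined data validity. Taken literally, the text gives either a void coin flip with both arms in one class, or a selection of analysed children by data completeness. This needs correcting before any child is allocated. Under the milder reading of valid data as baseline data, the risk of selection bias shrinks but the conflict of unit remains.

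The size of any selection bias cannot be computed from the document. The imbalance figures rest on an assumed class count and on unpaired flips. The power range rests on an assumed ICC. The contradiction depends on none of these.

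**What to change.** - Use one allocation step with the class as the unit, and say so in the Abstract and in Design and Procedures.
- Draw half the classes in each school to each arm (as near half as an odd number allows) in place of a coin per class.
- Obtain consent and complete baseline before the arm is revealed, and hold the experimental-group parent workshop after that.
- Delete the second software step and the valid-data condition.
- Analyse every consenting eligible child in the arm of the class, with school as a stratum and a class-level term or a small-sample cluster method. The exclusions for absence from sessions and for missing data must be brought into line with this.

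The draw and the wording cost little, and moving the workshop changes the schedule. The real cost is power: the 88 per group has no class term, so the stated 95% must be restated for class allocation and will be lower. Whether more classes are needed depends on an ICC that the sponsor must justify.

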## Materials and Equipment

Exclusion criteria for participants will be as follows: (1) less than 7 years and more than 9 years old; (2) use of psychoactive drugs; (3) absent from interventions (in which cases data from this participant will be excluded from analysis, but they will continue to participate in the intervention) and (4) diagnose of sleep disturbance or any health problems, such as neurological disorders, and psychiatric, cardiovascular or genetic diseases. Thus, to characterize the sample and to verify inclusion criteria questionnaires and scales will be applied, and strategies developed by researchers with parents/guardians and their children. These measures and the serious game itself are described below.

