#### Sleep Diaries

Sleep diaries are an extremely helpful tool to assess sleep patterns (Carney et al., 2012). We adapted a model of a diary and each page contains questions about children’s sleep for each day, forming a booklet that will be answered by the parents over 10 days. It will provide information about: (1) sleep and wake-up times, (2) sleep latency (amount of time taken from bedtime until the child falls asleep), (3) number of awakenings during the night, (4) total sleep time, and (5) naps timing and duration. Additionally, it was included questions on: activities before bedtime, how the child woke up and why; and parent’s perception of wellbeing of their child after each night of sleep. These measures will be registered over the 10 nights, allowing the researchers to examine the children’s habitual sleep patterns in weekdays and weekend.

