## Stepwise Procedures

### Participants

This study aims to recruit 176 healthy children enrolled in two private schools from Natal (Rio Grande do Norte – Brazil), as the number of children per class in these educational institutions ranges from 23 to 28. Schools will be selected by convenience, as there are difficulties to promote parental and school involvement (Jones et al., 2013; Wilson et al., 2014; Mindell et al., 2016), due to the concern of staff and parents about the activities developed in school and the necessity to adjust the research schedule to that of school activities, such as evaluation periods, vacation, science fair or school games. Furthermore, sample size was carried out using G^∗^Power 3.1.9, with alpha level of 5%, effect size of 0.5, and power of 95% for the two groups (Faul et al., 2007; Aberson, 2015). Results from this analysis indicated 88 participants to each group.

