Upon enrolment, the four stages of research will be followed, counting on the participation of children and their parents/guardians. All encounters with parents/guardians will happen at 6:40 pm, after the children’s classes, due to the parent’s convenience. First, during the stage of pre-intervention, questionnaires and scales will be applied to assess sociodemographic data, and characterize sleep habits and sleep pattern, by filling out the UNESP sleep habits and hygiene scale (child version) and sleep diary, besides giving the actiwatch to be wore by the children. Parents will also answer the Sleep Disturbance Scale for Children to identify the presence of sleep disorders. After this, parents from experimental group will participate in a workshop conducted by the research team about sleep habits and the importance of healthy sleep in childhood. The team will be available for an additional encounter 1 week after evaluation to clarify doubts about filling in the sleep diary and/or use of actiwatch.

The children themselves will be active in the evaluation steps. All evaluations with them will occur on the first Monday after each meeting with parents, once research begins with the parent’s authorization. In this stage, the children will answer the Pictorial Sleepiness Scale of Maldonado to evaluate sleepiness levels and will characterize their bedroom and the activities that they do before sleep at night, using, respectively, the strategies “Set up your bedroom” and “Mapping activities before bedtime.”

After pre-intervention evaluation, the experimental group will be submitted to the intervention with our serious game “Perfect Bedroom: learn to sleep well,” which will be conducted by three researchers during the children’s classes, at 02:00 pm on Tuesdays and Thursdays (see section “Intervention”).

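### After classes are assigned by coin, a second random draw is limited to children with valid data, so group membership or the analysed set can depend on what happens after allocation

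*Protocol article*

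**What the plan says.** All references are to the protocol article.

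- **First draw (Design and Procedures).** A coin is tossed for classes: "The first will select which classes will compose the experimental and control groups in each school".
- **Second draw (same paragraph).** An online random-assignment function "will be used to allocate participants of each class with valid data for analysis to each group". The paragraph does not say when this happens or what makes data valid.
- **Unit of allocation (same section, list of steps).** The first step is described as "randomization of participants to allocate each one in experimental or control group", which names the child and not the class.
- **Who is analysed.** Two rules are given. Materials and Equipment lists as an exclusion criterion children "absent from interventions (in which cases data from this participant will be excluded from analysis, but they will continue to participate in the intervention". Design and Procedures adds: "Missing data will result in individuals being excluded without outcome".
- **Group-specific action.** Within the pre-intervention stage, once the questionnaires, diary and actiwatch have been described: "After this, parents from experimental group will participate in a workshop conducted by the research team".
- **Target size (Participants).** "Results from this analysis indicated 88 participants to each group", from classes of 23 to 28 children in two schools.

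**The concern.** Randomisation protects a comparison only if membership of the groups is settled before anything that allocation could influence. A draw restricted to children with analysable data puts a filter inside the allocation procedure. If that filter uses information that arises after allocation, the groups compared are no longer the groups that chance formed.

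The filter can also work differently in the two arms. Only the experimental arm has game sessions during the evaluation period. Control children receive the intervention after all evaluations are complete (Ethics Statement), so they cannot be removed for missing it. The experimental arm could be reduced to its attenders while the control arm is not.

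Separately, the second draw has no clear function. Once a class has been assigned, its children already belong to an arm.

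**Working it through.** The point rests mainly on the text, so the passages are set side by side first. The arithmetic that follows only illustrates a possible size.

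**1. What can valid data mean, and what follows in each case?**

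| Reading | When it is known | Consequence |
|---|---|---|
| Complete data and attendance at the game | After the intervention or later | The draw decides the groups, or who is analysed, on post-allocation information |
| Complete baseline diary and actigraphy | After the recording period | Harmless only if no group-specific step has yet occurred |
| Eligibility shown by the baseline questionnaires | At the first parent meeting | Filtering is harmless, but the draw is still redundant or contradictory (step 2) |

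The first reading matches the only two analysis rules that the article states. On the second, the diary is a booklet, "forming a booklet that will be answered by the parents over 10 days". The workshop for experimental parents is described straight after the meeting at which diary and actiwatch are handed out, and before the extra meeting one week later for queries about them. That order suggests, without proving it, that group membership is acted on while baseline recording is still under way.

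**2. What can a second draw do within an assigned class?** There are two possibilities. It can choose a subset of the class, which leaves children out. Or it can send some children to the other arm, which overrides the coin. It can form no legitimate new groups on any of the three readings.

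**3. The plan's own figure.** Inputs from Participants: effect size 0.5, alpha 5%, power 95%, equal groups.

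- Normal approximation, one-sided: n = 2 × (1.645 + 1.645)² / 0.5² = 86.6, so 87. With the noncentral t distribution: 88.
- Two-sided: n = 2 × (1.960 + 1.645)² / 0.5² = 104.0, so 104. With the noncentral t distribution: 105.

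The stated 88 is therefore reproduced as a one-sided t-test. Sidedness is a separate matter and does not affect this point.

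**4. Illustration of a cut to 88.** Assumptions that the article does not state: four classes per arm, every child participating with valid data, and the second draw used to reach exactly 88.

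- Three classes hold at most 3 × 28 = 84, fewer than 88, so four are needed.
- Four classes hold 4 × 23 = 92 to 4 × 28 = 112.
- Children omitted per arm: 92 − 88 = 4 (4/92 = 4%) to 112 − 88 = 24 (24/112 = 21%).
- Widening of confidence intervals: √(92/88) = 1.02 to √(112/88) = 1.13, treating children as independent, although whole classes are assigned.
- The surplus vanishes once the share of children with valid data falls to 88/92 = 96% in the smallest case or 88/112 = 79% in the largest.

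**The case against.** **Timing.** A reader might infer that the groups are fixed only after outcomes are known. The article does not say so. It lists randomisation as the first step, gives no time for the second draw, and says in Materials and Equipment that questionnaires serve to check eligibility. The flow chart (Figure 2) is not shown and may settle the order. This stands: late timing is a possible reading, not a stated fact. It does not rescue the wording, because the benign reading still leaves a draw with no legitimate function.

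**A cut to 88.** A reader might also infer that surplus valid children are discarded to reach 88 per arm. The 88 is a recruitment target, the text speaks of allocating and not of reducing, and the number of classes is not given. This stands too. Participants and Anticipated Results both mention difficulty in securing or keeping parental involvement, so there may be no surplus at all. The figures in step 4 are an illustration only.

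**Source of the bias.** A purely random draw among valid children within an arm costs precision and adds no bias beyond that of a complete-case analysis. The arm-dependent selection comes mainly from the absence and missing-data rules, which would remain if only the draw were struck. This is correct and shapes the fix.

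**Randomising before any baseline data.** A reader might take this to be the natural remedy. It is unnecessary and would do harm: eligibility is checked with the baseline questionnaires, so allocating earlier would create exclusions after randomisation.

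**Conclusion.** The concern holds as a fault in a stated rule, not as a missing detail. The second draw is conditioned on analysable data, and the article's only criteria for entering the analysis are known after allocation. One of them, absence from the game, can apply only to the experimental arm. As written, group membership or the analysed set can depend on post-allocation data. On the most favourable reading the draw still either omits children or contradicts the class assignment, so the text has to change in any case.

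The size of any bias cannot be derived from the document. The loss of precision ranges from none, where there is no surplus, to intervals about 13% wider under the assumptions of step 4.

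**What to change.** 1. Delete the second draw together with its validity condition. Define the analysed groups as all consenting, eligible children in the arm to which their class was assigned, with no later equalising of numbers.
2. If individual allocation is what is meant, drop the coin step instead. Run the software once on the list of consenting children, after the eligibility checks and before any group-specific step such as the parent workshop.
3. In either case, make the list of steps in Design and Procedures name the same unit of allocation as the procedure.
4. Align the absence exclusion (Materials and Equipment) and the missing-data exclusion (Design and Procedures) with analysis as allocated. Keep absent children in their arm for the main comparison and state how missing outcomes are handled. A restricted set of attenders can be reported as a secondary analysis.

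Items 1 to 3 change wording only and need no further data collection. With class allocation the arms may be unequal in size, which the analysis can handle. Item 4 costs more, because it requires a chosen approach to missing data. Without it the arm-dependent selection remains.

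### The experimental-group parent workshop falls inside the pre-intervention stage, so the arm is disclosed and part of the intervention delivered before the 10-day baseline is complete

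*Protocol article*

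**What the plan says.** All references are to the protocol article.

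**Allocation (Design and Procedures).** "After selecting the schools by convenience, experimental and control groups are selected by two processes of randomization". The first is a coin toss for whole classes: "The first will select which classes will compose the experimental and control groups in each school". The second uses an online randomiser that "will be used to allocate participants of each class with valid data for analysis to each group".

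**Pre-intervention stage (Design and Procedures).** The text continues: "Upon enrolment, the four stages of research will be followed". Parents complete the sociodemographic questionnaire, the UNESP sleep habits scale and the sleep diary, and receive the actiwatch. "Parents will also answer the Sleep Disturbance Scale for Children to identify the presence of sleep disorders". The next sentence reads: "After this, parents from experimental group will participate in a workshop". A further encounter one week after the evaluation is offered for questions about the diary and the actiwatch. The children's own assessments take place on the first Monday after each parent meeting. The game sessions begin after the pre-intervention evaluation.

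**Baseline windows (Sleep Diaries; Actigraphy).** Parents keep the diary for 10 days, and the child wears the actiwatch over the same period.

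**Eligibility (Materials and Equipment).** Exclusions include "diagnose of sleep disturbance or any health problems", and "to characterize the sample and to verify inclusion criteria questionnaires and scales will be applied".

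**Use of the baseline (Controlling for Covariates; Intergroup and Intragroups Analysis).** Homogeneity of the arms is tested on demographic and sleep variables. The comparison goes ahead once no significant difference is found. Post-minus-pre differences and percentage changes are calculated for all numeric variables.

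**The concern.** A baseline should be measured before anyone has received any part of the intervention and, ideally, before anyone knows the arm. Here one arm's parents are taught about sleep habits at the start of the period in which they record their child's baseline sleep. They may change bedtimes at once, watch the child more closely, or fill in the diary as they have just been taught. The Anticipated Results section itself warns that parent reports may reflect social desirability.

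Two uses of the baseline are at stake. A contaminated baseline can fail the homogeneity test, or pass it while still being shifted. A change score that starts from a contaminated value mismeasures the effect. If sleep has already improved during the baseline window, change in the experimental arm is understated. If the workshop makes parents report more problems, change is overstated. The direction is therefore not known in advance.

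**Working it through.** **Step 1: order of events in the pre-intervention stage, as written.**

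| Event | Timing in the text |
|---|---|
| Questionnaires, UNESP scale, Sleep Disturbance Scale | Parent meeting, before the workshop |
| Diary and actiwatch started | Parent meeting; each then runs 10 days |
| Workshop, experimental-group parents only | Directly after the items above |
| Children's sleepiness scale, bedroom and activity tasks | First Monday after the parent meeting; the sleepiness scale runs over six class days |
| Help with diary and actiwatch | One week after the evaluation |
| Game sessions | After the pre-intervention evaluation |

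The help encounter comes at about day 7 of a 10-day record, so some three days of recording remain. The parent contacts counted in Design and Procedures are three evaluation meetings and three help encounters; no separate workshop evening is counted. If the workshop shares the first meeting, it precedes essentially all of the 10 nights. If it shares the help encounter, it falls within them. On either reading it comes before the diary and actigraphy end. On the first reading it also precedes the children's Monday tasks.

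**Step 2: what this establishes.** A workshop for one arm requires that the arm is already assigned and visible to those parents. This follows from the workshop sentence alone and does not depend on the order of paragraphs. The UNESP and Sleep Disturbance scales are listed before the workshop, so its content cannot affect them. They are exposed only if parents already know the arm.

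**Step 3: the plan's own figure.** Effect size 0.5, alpha 5%, power 95%, equal groups (Participants). The exact t calculation gives 87.26, so 88 per group, for a one-sided test; power at 88 is 95.1%. A two-sided test needs 104.9, so 105 per group; 88 gives 91.0%. The stated 88 therefore reproduces as a one-sided calculation. Both versions are shown below.

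**Step 4: illustration for change scores.** Assumptions, none from the documents: the workshop moves the experimental-arm baseline by b SD in the favourable direction, the true difference in change is 0.5 SD, and the SD is unaltered. The observed difference in change is then 0.5 − b.

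| b (SD) | 0.5 − b | Power, one-sided, 88 per group | Power, two-sided |
|---|---|---|---|
| 0 | 0.5 | 95% | 91% |
| 0.1 | 0.4 | 84% | 75% |
| 0.2 | 0.3 | 63% | 51% |
| 0.3 | 0.2 | 37% | 26% |

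**Step 5: illustration for the homogeneity test.** With the same shifts, a two-sided 5% t-test of the baseline at 88 per group is significant with probability 10% (b = 0.1), 26% (b = 0.2) or 51% (b = 0.3). A shift of 0.2 SD would thus pass unnoticed about three times in four (1 − 0.26 = 0.74). When it is noticed, the stated condition for starting the comparison is not met.

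Steps 3 to 5 ignore clustering by class.

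**The case against.** **Order is partly inferred.** No sentence dates the coin toss relative to consent, enrolment or screening. The numbered steps in Design and Procedures are not chronological, since the pre-intervention evaluation appears in the last item, after the intervention. The flow chart is not available here, and an article may leave the consent and concealment sequence to the full protocol. This stands. A reader might infer that classes are certainly tossed before enrolment, so that consent and exclusions differ by arm. The text order suggests that sequence but does not state it. The second randomisation step, applied to children with valid data, could even be read as later assignment.

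**Eligibility instruments precede the workshop.** This also stands, and nothing says that parents know the arm when they complete them. The control group receives the intervention after all evaluations (Ethics Statement), which weakens any motive for arm-related refusal. A one-arm loss of the worst 5% or 10% of a normal score would shift its mean by 0.109 or 0.195 SD. That is an upper-bound assumption: it supposes no comparable loss in the other arm and a perfect correlation between screening and outcome. It should not be read as the size of this problem.

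**The workshop might follow the completed diary.** The words introducing it could mean after the full 10 days, on an evening that is not counted. This is possible but not stated. The one-week help encounter is described after the workshop, and no extra evening appears in the tally.

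**The direct comparison of arms after the intervention does not use the baseline value.** This is correct. The t-tests at post-intervention and follow-up are not biased by a shifted baseline, although they are conditional on the homogeneity check. The damage is to that check, to the pre-intervention comparison, and to the within-arm and change analyses.

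**Conclusion.** The concern holds in this form: as written, an experimental-arm workshop within the pre-intervention stage discloses the arm and delivers sleep education before the 10-day diary and actigraphy are complete, and probably before the children's baseline tasks. The baseline of the secondary sleep parameters and of the children's tasks is exposed. The UNESP scale, which measures the primary outcome of sleep habits, is exposed only if parents already know the arm.

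The size cannot be taken from the documents. Under the stated assumptions, a favourable baseline shift of 0.1 to 0.3 SD removes 20% to 60% of a 0.5 SD difference in change (0.1/0.5 to 0.3/0.5), and an unfavourable shift would inflate it. Baseline testing is a poor safeguard at these sizes.

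Arm-dependent consent or exclusion remains possible but is not established. The document should state when the toss occurs relative to consent and screening, and reconcile the class toss with the second allocation step. The change is cheap and removes an avoidable bias, so it should be made.

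**What to change.** Rewrite Design and Procedures to give one explicit sequence for all classes in both schools:

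1. Obtain consent and complete eligibility screening.
2. Complete all baseline measures: parent scales, the full 10-day diary and actigraphy, and the children's sleepiness scale and sticker tasks.
3. Fix the list of eligible children.
4. Toss classes to arms, and only then reveal the arm.
5. Hold the experimental-group parent workshop, then start the game sessions.

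State that no exclusion on baseline eligibility is made after step 4. Say what the second randomisation step does, or delete it, so that there is a single unit and time of allocation.

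**Cost.** One parent evening is moved or possibly added, and there is a short delay between the end of baseline and the first game session. An added evening is not free, because the protocol names parental participation and school scheduling as difficulties. Sample size and instruments do not change.
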